### Balance criteria:

The following variables that are expected to be important correlates of the primary outcome and on which we wish to achieve balance were based on a data collected in 2009 in the same study clusters and over the same study period i.e. July to December.

1. Harmonic mean. For a given number of clusters and overall sample size maximum statistical efficiency is obtained if an equal number of patients per cluster are selected. The total sample size of 1500 across 22 clusters would require an *arithmetic* mean of 68 patients per cluster. However, due to the huge variability in the proportion of patients seen with suspected diarrhoea, URTI and malaria (when CHWs are likely to use RDTs) per cluster this approach was not seen as appropriate for several reasons including time to reach sample size quota, and cluster representation. Hence the sample size was weighted according to the cluster proportion of patients seen with suspected diarrhoea, URTI and malaria to achieve a *harmonic* mean of 68 patients per cluster in each arm. Since the sample size calculation was done before randomisation the overall harmonic mean (for all clusters) was used but this does not guarantee a harmonic mean of 68 per arm and therefore this was included as a restriction factor in the randomisation.
2. Total sample size. The precision and power of a study are usually maximised when sample sizes are similar in the treatment arms. In CRTs this means that the number of clusters as well as the number of individuals should be similar across treatment arms. Therefore, due to the variability in sample size per cluster this was also added as a restriction factor.
3. Number of health posts. There is a substantial amount of variation in the number of health posts per cluster from 2 to 26. Clusters (clinics) with bigger catchment populations have more health posts and therefore by balancing on this factor and equal sample size per arm will be achieved.

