## Sample Size and Statistical Methods:

### Sample Size Assumptions:

Key parameters and assumptions used to calculate the sample size are listed below:

- Number of clusters (clinics): 22
- Number of Health Posts: 207
- Number of CHWs: 414
- Expected difference in primary outcome in Phase 1 (40%):
  - Arm 1 - Non-intervention: 10% correctly treated vs.*
  - Arm 2 – RDT: 50% correctly treated*
- Expected difference in major secondary outcome (in phase 1):
  - Proportion of Pf positive patients receiving ACT: 0.5% in arm 1 vs. 50% in arm 2.*
  - Proportion of malaria negative patients treated with antimalarial: 90% in arm 1 vs. 50% in arm 2*
  - Proportion of malaria negative patients treated with antibiotic: 5% in non-intervention arm, 15% in RDT arm.
- Expected difference in primary outcome in Phase 2 (20%):
  - Arm 2 – RDT: 50% correctly treated.
  - Arm 3 – RDT extended programme: 70% or greater are correctly treated.
- Expected differences in major secondary outcome (in phase 2):
  - Proportion of Pf positive patients receiving ACT: 50% in arm 2 vs. 85% in arm 3.
  - Proportion of malaria negative patients treated with anti-malarial: 50% in RDT arm, 25% in RDT extended programme arm.
  - Proportion of malaria negative patients treated with antibiotic: 15 % in RDT arm, 20% in RDT extended arm.
- Sub-group analysis assumes that 40% of patients are under 10yrs*.

* estimates are based on initial results from the current randomised trial, based on data from 22 clinics in Afghanistan. There are no estimates in this region for effectiveness at CHW level.

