### Sample size:

An initial sample size of 1500 was selected for phase I to assess the secondary outcome of number of malaria positive patients correctly treated. Because Pf malaria is rare, the study is not powered for assessing the proportion of Pf cases correctly treated, although this will be examined as an exploratory analysis. For Phase II an initial sample size of 4000 individuals would assess the same secondary outcome, adjusted for cluster sampling. The confidence level (alpha) is 0.05 and the power (beta) is 0.8.

The sample size for both phases is adjusted for both intra-cluster variation (intra-cluster correlation coefficient of 0.5). To give a harmonic mean (see section 2.5.3) of 68 patients per cluster for phase I and 182 for phase II sample sizes of 2542 and 6792 are required in phase I and phase II respectively. This step is discussed in more detail in section 2.5.3.

|  |  | **Phase I** | | **Phase II** | |
| --- | --- | --- | --- | --- | --- |
| **Clinic** | **Province** | **SS weighting by cluster size** | **SS Weighted by cluster size for harmonic mean of 68** | **SS weighting by cluster size** | **SS Weighted by cluster size for harmonic mean of 182** |
| Ajighan | KDZ | 73 | 124 | 194 | 330 |
| AngorBagh | KDZ | 163 | 276 | 435 | 739 |
| ArbabRamazani | KDZ | 15 | 25 | 41 | 70 |
| BolaQachi | KDZ | 66 | 112 | 175 | 297 |
| CharSari | KDZ | 52 | 88 | 138 | 234 |
| Khan Abad | KDZ | 147 | 249 | 392 | 666 |
| KhwajaGhaltan | KDZ | 66 | 112 | 176 | 299 |
| Madrasa | KDZ | 30 | 51 | 80 | 136 |
| Nick Pay | KDZ | 12 | 20 | 33 | 56 |
| SandoqSai | KDZ | 63 | 107 | 169 | 287 |
| Baro | NGR | 37 | 63 | 100 | 170 |
| Batikot | NGR | 121 | 205 | 322 | 547 |
| Behsood | NGR | 72 | 122 | 191 | 324 |
| Chardhi | NGR | 21 | 36 | 55 | 93 |
| GardiGhos | NGR | 77 | 130 | 206 | 350 |
| Khewa | NGR | 109 | 185 | 290 | 493 |
| LandaBuch | NGR | 56 | 95 | 150 | 255 |
| MamandDara | NGR | 84 | 142 | 224 | 380 |
| NajmulQura | NGR | 67 | 114 | 178 | 302 |
| Rodat | NGR | 12 | 20 | 31 | 53 |
| SangarSarai | NGR | 68 | 115 | 181 | 307 |
| Shegay | NGR | 89 | 151 | 238 | 404 |
| Sample Size | | 1500 | 2542 | 3999 | 6792 |
|  |  |  |  |  |  |
| Arithmetic Mean | | 68.1818182 | 115.5455 | 181.7727273 | 308.7273 |
| Harmonic Mean | | 40.1240439 | 67.61738 | 107.1515805 | 182.1944 |
| Ratio (arithmetic:harmonic) | | 1.69474 |  | 1.69853 |  |

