### Statistical Methods:

An analysis plan will be developed by the investigators uring the trial. This will be reviewed by the statistician and DSMB prior to use. Broadly, primary and secondary outcomes will be assessed for differences by intervention arm using proportions with appropriate measures of statistical significance, for example chi^2^ test or Fisher’s exact test. Multivariate analysis will be conducted using a variety of potential explanatory variables related to the prescriber and the patients. These parameters are:

- Prescriber variables: Training history (prior to the intervention), age, gender.
- Patient variables: Age, gender, severity of symptoms, range of symptoms.
- Health system variables: clinic type, place of diagnosis and treatment (CHW or clinic).

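### The sample size rests on a harmonic mean, which suits near-equal clinic weights, but the only tests named are patient-level ones that ignore clustering and weight clinics by quotas of 20 to 276

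*Protocol*

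**What the plan says.** Section 2.5.3 explains that equal numbers per clinic were judged impractical, so "the sample size was weighted according to the cluster proportion of patients seen" with the main target conditions. Section 2.8.3 then scales these caseload-proportional quotas up "To give a harmonic mean (see section 2.5.3) of 68 patients per cluster for phase I and 182 for phase II". This takes Phase I from 1500 to 2542 patients and Phase II from 4000 to 6792. The Phase I quotas run from 20 (Rodat, Nick Pay) to 276 (AngorBagh). The harmonic mean per arm was also a restriction in the randomisation.

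The same section gives an "intra-cluster correlation coefficient of 0.5" and states: "The confidence level (alpha) is 0.05 and the power (beta) is 0.8". It says that 1500 was chosen for a secondary outcome in malaria-positive patients.

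Section 2.8.4 defers detail to an analysis plan. In outline, "primary and secondary outcomes will be assessed for differences by intervention arm using proportions with appropriate measures of statistical significance", with the chi-squared and Fisher's exact tests as examples. It names no clinic-level summary, clinic weight or clustered test.

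**The concern.** The sizing and the outlined analysis point to different estimators. The harmonic mean enters the variance of an equally weighted mean of clinic proportions. An arm proportion over all patients instead weights each clinic by its quota, and the harmonic mean does not describe its precision. At an ICC of 0.5 a clinic with 20 patients carries almost as much information as one with 276: the per-clinic variance factors are 0.5 + 0.5/20 = 0.525 and 0.5 + 0.5/276 = 0.502. Weighting by quota therefore wastes clinics, which are the scarce resource.

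Two things are at stake. Used as named, the tests treat patients as independent and give far too many false positives. If the analysis plan repairs only the standard error and keeps pooled proportions, the loss of precision from unequal weights remains. The 1042 extra patients in Phase I (2542 − 1500) and 2792 in Phase II (6792 − 4000) would then have been enrolled to reach a quantity that the analysis does not use.

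**Working it through.** **Inputs.** From section 2.8.1: "Number of clusters (clinics): 22", and Phase I rates "Arm 1 - Non-intervention: 10% correctly treated vs" "Arm 2 – RDT: 50% correctly treated". From section 2.8.3: the quotas, ICC 0.5 and alpha 0.05 (taken as two-sided, which the protocol does not state). From Table 3: the Phase I allocation, 11 clinics per arm.

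**The plan's own figures.** Harmonic mean = 22 / Σ(1/m). The Phase I quotas sum to 2542 with harmonic mean 67.62. The Phase II quotas sum to 6792 with harmonic mean 182.19. Also 1500 × 1.69474 = 2542.1. By arm, the totals are 1280 and 1262 and the harmonic means 66.03 and 69.28, as in Table 4. All of these reproduce.

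**Tests as named.** The design effect for a pooled proportion is 1 + ρ(Σm²/Σm − 1).
- No RDT: Σm² = 201,474, so 1 + 0.5 × (157.40 − 1) = 79.2.
- RDT: Σm² = 191,896, so 1 + 0.5 × (152.06 − 1) = 76.5.

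The true standard error is thus about √78 = 8.8 times the one that chi-squared assumes. The 1.96 limit then acts like 1.96/8.8 = 0.22, which is exceeded in about 82% of null trials. A beta-binomial simulation (20,000 runs, actual quotas) gives 83% at ICC 0.5, 76% at 0.25 and 63% at 0.1. A t test on clinic proportions in the same runs rejects in 3% to 5%.

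**Pooling with a cluster-corrected variance.** Effective clinics = (Σm)²/Σm².
- No RDT: 1280²/201,474 = 8.13.
- RDT: 1262²/191,896 = 8.30.
- Two clinics supply 36% of each arm: (276 + 185)/1280 and (249 + 205)/1262.

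Variance per arm (HM = harmonic mean, N = arm total):
- Equal clinic weights: p(1−p)[ρ/11 + (1−ρ)/(11·HM)]
- Pooled: p(1−p)[ρ·Σm²/(Σm)² + (1−ρ)/N]

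Phase I at ICC 0.5:
- Equal: 0.09 × (0.04545 + 0.00069) + 0.25 × (0.04545 + 0.00066) = 0.00415 + 0.01153 = 0.01568; SE 0.125
- Pooled: 0.09 × (0.06148 + 0.00039) + 0.25 × (0.06024 + 0.00040) = 0.00557 + 0.01516 = 0.02073; SE 0.144
- Variance ratio: 0.02073/0.01568 = 1.32

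Power for a difference of 0.40 in Phase I, from the noncentral t on 20 df:

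| ICC | Equal weights | Pooled | Variance ratio |
|---|---|---|---|
| 0.5 | 86% | 75% | 1.32 |
| 0.4 | 92% | 84% | 1.32 |
| 0.25 | 99% | 96% | 1.30 |
| 0.1 | >99% | >99% | 1.25 |

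At ICC 0.5 the normal approximation gives 89% and 79%, and the simulation 84% and 77%. Inverse-variance clinic weights also give 86% (t).

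Phase II (50% vs 70%), with the Phase I allocation as a stand-in: SE 0.145 vs 0.168, variance ratio 1.34, power 26% vs 21% at ICC 0.5; 82% vs 71% at ICC 0.1.

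**The case against.** The strongest objection is that the protocol does not fix a pooled estimator. Section 2.8.4 is worded as a broad outline, offers its tests as examples and leaves the detail to an analysis plan. Section 2.5.2 mentions cluster-level analysis when discussing imbalance, and the harmonic-mean sizing itself suggests that clinic summaries may be intended. This stands: pooling is what the named tests imply, not a rule laid down.

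A reader might also infer that the protocol's 0.8 power is lost. The documents do not support that. The 0.8 sits with a secondary outcome in malaria-positive patients, and no positivity rate is given, so it cannot be checked. The 75% belongs to a pooled analysis with a cluster-adjusted variance, which the protocol never names. With the tests it does name, power does not fall (about 99% in the simulation); the type I error rises. The Phase I shortfall also depends on the ICC: pooled power is already 84% at ICC 0.4.

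Nor is the harmonic mean useful only under strictly equal weights, since inverse-variance weights do as well. The Phase II figures are approximate because clinics are re-randomised. Over simulated re-randomisations, pooled power ranged from 20% to 23% at ICC 0.5 and from 68% to 76% at ICC 0.1. At ICC 0.5 Phase II is underpowered whatever the weights.

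Finally, section 2.6.1 defines the outcome as a proportion of patients, so moving to clinic means changes the target. That is a real cost. None of this removes the mismatch between the sizing and the only tests named.

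**Conclusion.** The concern holds as a mismatch between sizing and outlined analysis. The protocol sizes for clinics that count about equally and then gives as examples only tests that ignore clustering and weight clinics by quota.

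The more serious consequence is the type I error of the named tests, about 83% in Phase I at the stated ICC and still 63% at ICC 0.1. The second is the precision lost if only the standard error is corrected: about 8 effective clinics per arm instead of 11, and a Phase I variance 1.25 to 1.32 times larger for ICCs from 0.1 to 0.5. In power this is 75% instead of 86% at ICC 0.5, and little at ICC 0.25 or below.

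The power figures assume the primary-outcome rates, the planned quotas being met, two-sided 0.05 and 20 df without allowance for province. They illustrate the loss and do not show that the protocol's stated power is wrong.

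**What to change.** In section 2.8.4, replace the chi-squared and Fisher examples with a clinic-level primary analysis: the difference between arms in mean clinic proportion, with equal (or inverse-variance) clinic weights, stratified by province as in the randomisation, tested by a t test on the clinic summaries. Report pooled patient proportions by arm alongside.

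This matches the harmonic-mean sizing and needs no more patients. In the simulation the unstratified clinic-level t test kept the type I error at about 3% to 5%; taking out province costs one or two of the 20 degrees of freedom. The edit to the text is short, but the estimate then describes the average clinic rather than the average patient, and the protocol should say so.

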### Statistical Methods:

An analysis plan will be developed by the investigators uring the trial. This will be reviewed by the statistician and DSMB prior to use. Broadly, primary and secondary outcomes will be assessed for differences by intervention arm using proportions with appropriate measures of statistical significance, for example chi^2^ test or Fisher’s exact test. Multivariate analysis will be conducted using a variety of potential explanatory variables related to the prescriber and the patients. These parameters are:

- Prescriber variables: Training history (prior to the intervention), age, gender.
- Patient variables: Age, gender, severity of symptoms, range of symptoms.
- Health system variables: clinic type, place of diagnosis and treatment (CHW or clinic).

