### Randomisation Methods:

### Number of unrestricted allocations

The study is a stratified cluster randomised trial with a total of 22 clusters.

In Kunduz the total number of ways of allocating the 10 clusters to the two intervention groups, assuming equal number of clusters per arm:

$$\binom{10}{5}\binom{5}{5}=252$$

In Nangahar the total number of ways of allocating the 12 clusters to the two intervention groups, assuming equal number of clusters per arm

$$\binom{12}{6}\binom{6}{6}=924$$

Therefore in total there are: 252 x 924 = 232,848 possible allocations of 22 clusters into the 2 study arms after stratification.

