### Results of randomisation

The final choice of restriction criteria resulted in 1598 acceptable allocations from which one was randomly chosen. Table 2 and **Error! Reference source not found.** summarise the allocation process.

6 clinics (clusters) have been allocated to each study arm in the Nangahar stratum, and 5 per arm in Kunduz stratum. Study arm 0 denotes no RDT, and study arm 1 denotes RDT (intervention) – see next section.

Table 2: Results of intervention allocation process

| **Kunduz** | | |  | **Nangahar** | | |
| --- | --- | --- | --- | --- | --- | --- |
| **Cluster** | **Clinic** | **Study arm** |  | **Cluster** | **Clinic** | **Study arm** |
| 1 | Ajighan | 0 |  | 11 | Baro | 0 |
| 2 | AngorBagh | 0 |  | 12 | Batikot | 1 |
| 3 | ArbabRamazani | 0 |  | 13 | Behsood | 0 |
| 4 | BolaQachi | 1 |  | 14 | Chardhi | 1 |
| 5 | CharSari | 1 |  | 15 | GardiGhos | 1 |
| 6 | Khan Abad | 1 |  | 16 | Khewa | 0 |
| 7 | KhwajaGhaltan | 0 |  | 17 | LandaBuch | 0 |
| 8 | Madrasa | 1 |  | 18 | MamandDara | 1 |
| 9 | Nick Pay | 1 |  | 19 | NajmulQura | 1 |
| 10 | SandoqSai | 0 |  | 20 | Rodat | 0 |
|  |  |  |  | 21 | SangarSarai | 1 |
|  |  |  |  | 22 | Shegay | 0 |

Table 3: Summary of clusters allocated to study arms in Phase 1

| **Arm 0 (no RDT)** | **Arm 2 (RDT)** |
| --- | --- |
| Ajighan | Batikot |
| AngorBagh | BolaQachi |
| ArbabRamazani | Chardhi |
| Baro | CharSari |
| Behsood | GardiGhos |
| Khewa | Khan Abad |
| KhwajaGhaltan | Madrasa |
| LandaBuch | MamandDara |
| Rodat | NajmulQura |
| SandoqSai | Nick Pay |
| Shegay | SangarSarai |

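### The only tests named for the arm comparisons, chi-square and Fisher's exact, take no account of clinic clustering, which contradicts a 22-clinic stratified cluster trial sized with an ICC of 0.5

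*Protocol*

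**What the plan says.** Section 2.8.4 begins by deferring detail: "An analysis plan will be developed by the investigators" during the trial, to be reviewed by the statistician and the DSMB before use. It then sets the broad approach. Primary and secondary outcomes will be compared between arms "using proportions with appropriate measures of statistical significance, for example chi^2^ test" or Fisher's exact test. A multivariate analysis follows, with prescriber, patient and health-system covariates. The last group reads "Health system variables: clinic type, place of diagnosis and treatment (CHW or clinic"). Clinic as a cluster, province and Phase I arm are not mentioned.

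The design sections describe a different structure. Section 2.5.4 states "The study is a stratified cluster randomised trial with a total of 22 clusters". Section 2.5.5 reports that "6 clinics (clusters) have been allocated to each study arm in the Nangahar stratum, and 5 per arm in Kunduz stratum". Section 2.8.3 adjusts the sample size for an "intra-cluster correlation coefficient of 0.5" and adds that "The confidence level (alpha) is 0.05 and the power (beta) is 0.8". Cluster-level analysis is mentioned once, in section 2.5.2, as background to restricted randomisation. It does not set this trial's analysis.

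**The concern.** The clinic is the randomised unit, so an arm difference has to be judged against variation between clinics. A chi-square or Fisher test on pooled patients judges it against binomial variation among 2542 (Phase I) or 6792 (Phase II) patients, as though each had been randomised separately. If patients of one clinic resemble each other as strongly as the protocol assumes, the standard error is several times too small and a nominal 5% test is far from 5%. This affects the primary outcome and every secondary outcome that is a proportion compared between arms.

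The protocol itself treats type I error as a design concern. It built a validation matrix so that the restricted allocation would not disturb the 0.05 level. The named tests would undo that care.

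A smaller related matter is that place of diagnosis and treatment is listed as a covariate. It is settled after randomisation and RDT access may change it.

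**Working it through.** **Inputs.** Clinic quotas m are the weighted columns of the section 2.8.3 table. The allocation is Table 2. The ICC is 0.5 and alpha 0.05; sidedness is not stated, so two-sided is assumed. The Phase II allocation is not yet drawn, so the Phase I allocation is used for both phases.

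**The protocol's own figures first.** The quotas sum to 2542 and 6792, with harmonic means of 67.62 and 182.19, as printed. Table 2 gives Phase I arm totals of 1280 and 1262 and harmonic means of 66.03 and 69.28, as in Table 4. The inputs are therefore read correctly.

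**Design effect.** For an arm with M patients, the variance of the pooled proportion is p(1−p) × Σ m[1+(m−1)ICC] / M². Summing over both arms and dividing by the independence value gives D. As a check, the single-formula version is 1 + (m_w − 1) × ICC with m_w = Σm²/Σm.

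- Phase I: m_w = 393,370 / 2542 = 154.7, so 1 + 153.7 × 0.5 = 77.9. The arm-by-arm D is also 77.9.
- Phase II: m_w = 2,808,030 / 6792 = 413.4, so 1 + 412.4 × 0.5 = 207.2. The arm-by-arm D is also 207.2.

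**Type I error of the patient-level test.** This is 2[1 − Φ(1.96/√D)].

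- Phase I, ICC 0.5: √77.9 = 8.82; 1.96/8.82 = 0.222; rate 82%.
- Phase II, ICC 0.5: √207.2 = 14.39; 1.96/14.39 = 0.136; rate 89%.

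| ICC | Source | Phase I, formula | Phase I, simulated | Phase II, formula | Phase II, simulated |
|---|---|---|---|---|---|
| 0.5 | protocol | 82% | 83% | 89% | 90% |
| 0.2 | assumed | 73% | 73% | 83% | 83% |
| 0.1 | assumed | 63% | 63% | 76% | 76–77% |
| 0.05 | assumed | 51% | 50–51% | 67% | 67–68% |
| 0.01 | assumed | 22% | 22% | 39% | 39% |

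The simulations are 20,000 beta-binomial trials per setting with no arm effect and null proportions of 10% and 50%. Fisher's exact test, run on 300 trials per setting, is no better: about 82% and 89–92% at ICC 0.5.

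**If 0.5 was meant as a between-cluster coefficient of variation k.** Then ICC = k²p/(1−p). At p = 10% it is 0.25 × 0.1/0.9 = 0.028, with rates of 39% and 58%. At p = 50% it is 0.25, with rates of 75% and 85%.

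**Role of province.** Allocation was re-drawn within province, with an assumed province difference of 20% v 40%. The Phase I rate moves from 50% to 54% at ICC 0.05 and does not change at ICC 0.5. Only at ICC 0.01 is the addition marked (22% to 36%).

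**A valid alternative.** A linear model of the 22 clinic proportions on arm and province (22 − 3 = 19 df), in the same simulations, rejects 3.0% to 5.3% of the time across all these ICCs and both phases.

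**The case against.** The strongest reply is that the protocol does not commit to an unadjusted test. The approach is described as broad, the significance measures are to be appropriate, the two tests are examples, and a plan reviewed by the statistician and DSMB will follow. Patient-level is the natural reading of the text but not its wording, and choice of test is commonly left to an SAP. Elsewhere the protocol is plainly aware of clustering. All of this stands, so a reader who infers that the trial is bound to run an unadjusted patient-level analysis goes further than the text. It does not remove the point. Both examples have the same defect, the covariate list repeats the omission, and nothing tells the later author to allow for clinics.

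Other stronger readings are also not supported:

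- **A false claim of benefit would be the likely result under the null.** The rates above are two-sided. Null rejections favouring RDTs are about 41–42% in Phase I and 45–46% in Phase II at ICC 0.5, below one half.
- **The error rate is 50% or more whatever the ICC.** Only the ICC 0.5 figures rest on the protocol. The 50% figure needs an assumed ICC near 0.05, and at 0.01 the rates are 22% and 39%.
- **Every secondary outcome is affected in this way.** Time to treatment, costs, attendance counts and RDT accuracy are not proportions compared between arms, and these calculations do not cover them.
- **The covariate list biases the primary result.** The primary outcome concerns treatment by CHWs, so place of care hardly varies for it. Section 2.8.4 also does not say that the arm effect will be adjusted for these variables. The caution applies to outcomes that include clinic data.
- **Only a clinic-level linear model will do.** Mixed models or GEE with small-sample correction are also acceptable.

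**Conclusion.** The point holds as a contradiction within the protocol: the example tests do not fit the stratified cluster design or the ICC used to size it. Taken in their ordinary form, they would give a two-sided type I error of about 83% in Phase I and 90% in Phase II at the protocol's own ICC. These figures rest on the printed quotas, the Table 2 allocation (carried over to Phase II) and a two-sided 5% level. At the lowest ICC tried, 0.01, which is an assumption, the rate is still four to eight times nominal. Ignoring the clinics causes almost all of the inflation. Province belongs in the model because randomisation was stratified by it. The correction should be made before any arm comparison is run.

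**What to change.** In section 2.8.4, replace the chi-square and Fisher examples with a statement that all arm comparisons account for clustering by clinic and adjust for province. Suitable examples are a linear model of the 22 clinic proportions on arm and province (19 df), or a mixed model or GEE with small-sample correction. In Phase II, also include Phase I arm, because clinics are re-randomised within it; the clinic-level model then has 22 − 4 = 18 df.

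Provide separately for sparse outcomes, such as Pf cases treated with ACT. As a rough guide, apply each clinic's malaria share of treatments (section 2.8.2) to its Phase I quota, take 5–10% of malaria as Pf (section 1.2), and assume that treatments stand in for true cases. Then 13 of the 22 clinics expect fewer than one Pf case. At Chardhi, for example, 36 × 45/250 × 10% = 0.65. Report such outcomes descriptively, or use a method that tolerates clinics with no cases.

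For outcomes that include clinic-level data, do not adjust the arm effect for place of diagnosis and treatment.

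The cost is one paragraph, with no change to sites, conduct or data collection. The downside is wider confidence intervals, which reflect the information that 22 clinics can give.

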### Trial Arms:

**Phase I:**

*Arm 1: Non-intervention arm:*

The non-intervention arm will be based on the existing clinical diagnosis, pre-referral treatment and referral to a clinic in areas where RDTs have not been deployed at CHW level. Arm 1 CHWs will receive refresher training according to the National Strategy for CBMM which includes the current IMCI guidelines.

Vs:

*Arm 2: RDT Arm*

Provision of community level diagnostics by rolling out RDTs to CHWs through the national strategy for Community based Management of Malaria. The arm has been designed exactly as the current National guidelines for RDT implementation..The arm will include:

- Clinic level microscopy or RDT and CHWs using RDTs to provide parasitological diagnosis to diagnose, treat and/or refer patients. Under this scheme, CHWs will be provided with CQ, SP and artesunate (AS). Depending on the diagnostic result, they prescribe according to the National Treatment Guidelines (CQ for confirmed vivax, SP and AS for confirmed falciparum, and no antimalarial for a negative result).
- CHW training will be conducted exactly as described in the CBMM strategy, using a “trickle down approach” where Training of Trainers takes place at the central level for provincial trainers of local NGOS who run the health service. These, in turn, run workshops for training CHSs and CHWs (see section 2.2 for pre-evaluation of training and roll-out). Participants will receive training to enforce revised IMCI guidelines, taken from the CBMM strategy document, which include an RDT in the algorithm for fever (see annex 2).
- There are no plans for additional support or refresher training, and no plans for quality control and assurance contained in the National Plan.
- CHWs are not equipped with suitable storage facilities for the RDTs, for example evaporative coolers.
- Monitoring and evaluation takes place according to the draft strategy.

The second phase of the trial will be initiated in Feb 2012. The second phase of the trial will re-randomise clinics to either the RDT arm (as in arm 2, above) and a third arm (arm 3). The third arm will answer the question: “how can the performance of RDTs at community level be enhanced?”. The same set of outcomes will be used to measure the relative effectiveness of each approach. A revised random allocation using the same methods will be conducted for the Phase II randomisation.

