### Trial Profile:

**Figure: Trial schematic for Phase 1.**

If the criteria for running phase 2 of the trial are met the 22 clinics will be re-randomised so that 50% of those clinics in arm 1 are randomised to arm 3 and 50% to arm 2, and 50% of those in arm 2 will be randomised to arm 3 with 50% remaining in arm 2 (figure 2).

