### Trial Primary Outcome:

The primary outcome of the study is:

- Proportion of patients (in)correctly treated by CHWs.

Correct treatment is defined as:

- - Treatment of PCR confirmed Pf with SP/AS.
  - Treatment of PCR confirmed Pv with CQ (regardless of accompaniment with SP or addition of primaquine).
  - No antimalarial for PCR confirmed negative diagnosis.

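### The Phase II analysis outlined in 2.8.4 does not name the clinic's own Phase I result, or its Phase I arm, as a covariate, although the same 22 clinics are re-randomised on the same outcomes

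*Protocol*

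**What the plan says.** - **Same clinics (2.5.6 Trial Profile).** If Phase II goes ahead, "the 22 clinics will be re-randomised so that 50% of those clinics in arm 1 are randomised to arm 3 and 50% to arm 2". The clinics from Phase I Arm 2 are divided in the same way, so the second allocation is split within Phase I arm.
- **Same outcomes (2.5.1 Trial Arms).** "The same set of outcomes will be used to measure the relative effectiveness of each approach". The primary outcome is "Proportion of patients (in)correctly treated by CHWs" (2.6.1).
- **Same allocation method (2.5.1).** "A revised random allocation using the same methods will be conducted for the Phase II randomisation". The restriction criteria in 2.5.3 are total sample size, harmonic mean cluster size and number of health posts. None of them is an outcome.
- **Planning values.** 2.8.1 expects "Arm 2 – RDT: 50% correctly treated" and "Arm 3 – RDT extended programme: 70% or greater are correctly treated" in Phase II, and 10% correct in Arm 1 in Phase I. 2.8.3 uses an "intra-cluster correlation coefficient of 0.5" and a Phase II harmonic mean of 182 patients per clinic.
- **Analysis (2.8.4 Statistical Methods).** An analysis plan is to be written during the trial. In broad terms, proportions are compared by arm, with chi-square or Fisher's exact test as examples. Then "Multivariate analysis will be conducted using a variety of potential explanatory variables related to the prescriber and the patients". The named variables are prescriber training history, age and gender; patient age, gender and symptoms; and clinic type and place of diagnosis and treatment.

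**The concern.** Each clinic's Phase I proportion correctly treated is a baseline measurement of the Phase II primary outcome, taken before the second randomisation. The covariate list in 2.8.4 leaves it out. It also leaves out Phase I arm, the factor within which the second allocation is split.

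Two things are at stake. With 11 clinics per arm and an ICC of 0.5, the precision of the Arm 3 versus Arm 2 contrast is set almost wholly by variation between clinics, and the Phase I result is a direct measure of that variation already in the data. Second, 2.5.2 itself warns that with few clusters and strong between-cluster correlation, chance imbalance on correlates of the primary outcome can affect interpretation. The size-based criteria do not control earlier clinic performance, and the covariates now listed would not correct for it.

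**Working it through.** **Inputs from the protocol.** 11 clinics per arm; p = 0.50 and 0.70; ICC ρ = 0.5; m = 182; alpha 0.05, taken as two-sided (sidedness is not stated).

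**Input not in the protocol.** r, the correlation between a clinic's Phase I and Phase II proportions. 2.8.1 says there are no regional estimates of effectiveness at CHW level. A range from 0 to 0.9 is used.

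**1. The plan's own figures.** The weighted cluster sizes in 2.8.3 sum to 2542 and 6792, with harmonic means 67.6 and 182.2, as stated. The initial Phase II total of 4000 is not reproduced for the primary outcome: 93 per arm × design effect (1 + 181 × 0.5 = 91.5) × 2 arms = 17,019. The protocol ties the 4000, and its 80% power, to a secondary outcome (malaria-positive patients correctly treated) for which it gives no rates. So 80% is not a stated power for the primary contrast.

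**2. Share of variance between clinics.** ρ / [ρ + (1 − ρ)/m] = 0.5 / (0.5 + 0.5/182) = 0.995.

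**3. Unadjusted Phase II power.** Variance = [(0.5 × 0.5 + 0.7 × 0.3)/11] × (0.5 + 0.5/182) = 0.02102. SE = 0.145; noncentrality = 0.20/0.145 = 1.38. Power on 20 df is 26% (28% by normal approximation).

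**4. Adjusted power.** Multiply the variance by (1 − r²) and use 17-19 df. The lower end of each range adds a small-sample penalty for one covariate.

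| r | SE before penalty | t-based power |
| --- | --- | --- |
| 0 | 0.145 | 25-26% |
| 0.3 | 0.138 | 27-28% |
| 0.5 | 0.126 | 31-33% |
| 0.7 | 0.104 | 43-45% |
| 0.8 | 0.087 | 56-59% |

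Allowing for sampling error in the clinic proportions takes off about one more point (42% at r = 0.7, 55% at r = 0.8). Charging for Phase I arm as a second covariate, with no credit for any variance it explains, gives about 24% at r = 0, 30% at r = 0.5 and 40% at r = 0.7.

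**5. Weaker prediction in former non-RDT clinics.** Suppose r = 0.7 in former RDT clinics and 0 to 0.3 in the others. The mean of (1 − r²) over the two halves is 0.755 to 0.71, and t-based power is 29-31%.

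**6. Simulation.** Clinic rates were beta-distributed, with the 2.8.3 cluster sizes, the actual Phase I arms, and the Phase I result ranked within Phase I arm. At latent correlation 0.3 there was no gain; at 0.5 power went from 26% to 29%; at 0.7 from 25% to 34%; at 0.8 from 27% to 40%. Type I error, checked in one setting (correlation 0.7, ICC 0.5), was 4.7%.

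**7. Limits.** By normal approximation, 80% power needs variance (0.20/2.80)² = 0.0051, so 1 − r² = 0.0051/0.0210 = 0.242 and r ≈ 0.87. If the true ICC were 0.05-0.1, unadjusted power would already be 82-99%.

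**The case against.** The strongest reply is that this belongs to the analysis plan. 2.8.4 defers to one, speaks broadly, offers its tests as examples and calls the covariates potential ones. A single list serves both phases, and a Phase I result could not be a covariate in Phase I, so its absence is not a decision to exclude it from Phase II. Phase II is also conditional, and the content of Arm 3 awaits Phase I results. This stands in part. A reader might infer that the protocol treats the clinics as new units or rules out baseline adjustment. It says neither, and the split within Phase I arm shows that the first phase was considered in the design. What remains is that the protocol chose to name covariates, and the list omits the clearest candidate and the factor used in the split.

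A second reply is that the power is not free. This stands. The gain rests on an unstated r. Half the clinics were measured without RDTs, at an expected 10% correct, and prescribing without a test may predict prescribing with one poorly. Centring or ranking within arm removes the difference in level but not weaker prediction. 2.3 also provides for replacement CHWs, which could lower r.

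A third reply is that not every secondary outcome can be adjusted by its own Phase I value. This stands too. Arm 1 clinics have no RDT results, so RDT invalid rate, sensitivity and specificity have no Phase I value there. Falciparum cases are rare enough that many clinics may have none.

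**Conclusion.** The point holds as a cheap improvement to the stated analysis. The outline in 2.8.4 omits the clinic's Phase I result and Phase I arm, and at the protocol's own ICC a clinic-level baseline is the natural source of extra precision. The likely gain runs from nothing to moderate: from 26% to about 31-33% at r = 0.5 and 43-45% at r = 0.7, or 29-34% under the less favourable assumptions in steps 5 and 6. Below about r = 0.25 there is no gain, and at r = 0 the loss is 1-4 points (up to about 2.5 at ICC 0.5; 3-4 in simulation at ICC 0.2).

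A reader might also infer that adjustment would repair the power of Phase II. It would not: r of about 0.87 would be needed at ICC 0.5. The low power comes from 22 clinics at that ICC and is a separate matter. All these figures assume 50% against 70%, ICC 0.5, a two-sided test and the assumed r. With a much smaller ICC the point matters little.

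**What to change.** In 2.8.4, pre-specify the Phase II primary-outcome comparison of Arm 3 with Arm 2 as a clinic-level analysis, or one with a clinic random effect. Adjust it for province, Phase I arm and the clinic's Phase I proportion correctly treated, centred or ranked within Phase I arm because the arms are expected to differ (10% against 50%). Fix this before Phase II outcome data are seen, so that the covariate is not chosen afterwards.

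Extend it only to secondary proportions that have a usable Phase I value in every clinic. Leave out RDT invalid rate, sensitivity and specificity, and falciparum cases treated with ACT. Check small denominators first: Nick Pay and Rodat have Phase I quotas of 20, so at the assumed 40% under 10 years each would contribute about 0.4 × 20 = 8 children.

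The cost is a change of wording, with no new data for the primary outcome. The statistical cost is one or two degrees of freedom for the Phase I terms and a small loss of power if the phases prove uncorrelated.
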